## Interventions

### Dietary and exercise therapy

After entering the group, all subjects will adopt a unified control diet and exercise regimen that will remain unchanged in subsequent studies. In this study, to control total energy, for T2DM patients with greater than normal body weight, it is recommended to calculate the total energy according to 25 ~ 30 kcal/(kg · day) and then adjust to individual energy standard according to the patient’s height, weight, sex, age, activity, stress status, etc. A long-term very low-calorie diet (less than 800 kcal/day) is not recommended.

To cultivate a nutritionally balanced diet, protein intake should be 15 ~ 20% of total energy, fat intake should be less than 30%, and carbohydrate intake should be 45 ~ 60% of total energy.

Regarding the exercise regimen, at least 150 min of moderate-intensity aerobic exercise per week (50 ~ 70% of the maximum heart rate; maximum heart rate = 220 − age) should be performed for at least 3 days a week.

Please refer to “Expert consensus on comprehensive management of type 2 diabetes with obesity in China” for more information [13].

### Drugs and usage

#### The DDG combined with metformin group

One pack of DDG (*Atractylodes lancea* 18 g, *Atractylodes macrocephala* 18 g, *Salvia miltiorrhiza* 15 g, *Polygonum cuspidatum* 12 g, Folium ilicis cornutae 15 g, *Scutellaria* 12 g, *Linderae radix* 9 g) will be administered twice a day by bringing water to a boil, stirring, covering and sealing for 3 to 5 min before serving.

Metformin will be started at one tablet (0.5 g) once daily after dinner during the first week of treatment, titrated up to a maximum of two tablets twice daily (maximum dose metformin 2000 mg daily) over 4 weeks as tolerated with continuation until the end of treatment. The treatment will be conducted for 24 weeks, and patients will be followed up for 24 weeks.

#### The placebo combined with metformin group

One pack of placebo granules will be administered twice a day by bringing water to a boil, stirring, covering and sealing for 3 to 5 min before serving.

The metformin dose was the same as that in the DDG combined with metformin group.

The treatment will be conducted for 24 weeks and followed up for 24 weeks. Participants will return the unused tablets and bottle at each follow-up visit. Unused tablets will be counted and recorded on the appropriate CRF (case report form). Other hypoglycemic, lipid-lowering or weight-loss drugs were not allowed to be used during the trial.

DDG and placebo granules will be provided by Sichuan New Green Pharmaceutical Technology Development Co., Ltd. Metformin will be manufactured by Sino-American Shanghai Squibb Pharmaceutical Co., Ltd.

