### Subject screening and selection

For outpatients or inpatients who come to the hospital, if the diagnostic criteria for type 2 diabetes with obesity are met (as shown in Tables 1 and 2), the inclusion and exclusion criteria will be assessed (as shown below). Patients will not be recruited if any of the inclusion criteria are not met or if any of the exclusion criteria are met. If the patient meets one of the rejection criteria or termination criteria, they will be removed from the trial. Participants will be required to provide written informed consent to cooperate with the doctor’s treatment and follow-up and to provide information that does not exceed the scope of ethical approval. Participants who did not meet the requirements will be removed from the study. During this period, medical history, physical examinations, blood samples and medical records of participants will be collected and kept.

**Table 1 Tab1:** Diagnostic criteria for type 2 diabetes [13]

Standard of diagnosis	Glucose levels in intravenous plasma mmol/L
Typical diabetes symptoms (polydipsia, polyuria, polydipsia, weight loss) plus random plasma glucose testing	≥ 11.1
Fasting plasma glucose test	≥ 7.0
Plasma glucose measured 2 h after glucose load Repeat the test another day for no symptoms of diabetes	≥ 11.1

**Table 2 Tab2:** Diagnostic criteria for obesity [13]

Classification	BMI (kg/m^2^)
- Underweight	< 18.5
- Normal weight	18.5–23.9
- Overweight	24.0–27.9
- Obesity	≥ 28.0
For waist	(cm)
- Male	≥ 90.0
- Female	≥ 85.0

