#### Exclusion criteria [11]

Patients with nephrotic syndrome (urine protein exceeding 3.5 g/L per day), oedema or renal failure (serum creatinine over 115 μmol/L);Patients who have been diagnosed with heart failure (NYHA III-IV) or who have had a pacemaker implanted;Patients with liver dysfunction (aspartate aminotransferase and glutamate pyruvate transaminase levels twofold above the normal range) or a diagnosis of cirrhosis;Patients with high levels of HbA1C (greater than 9%);Pregnant or breastfeeding mothers, including mothers who have given birth within the last 24 weeks;Patients who require insulin therapy;Patients who receive other therapies or whose doses have changed during treatment;Patients with secondary obesity caused by other diseases, such as Cushing’s syndrome, primary hypothyroidism, hypothalamic obesity, polycystic ovary syndrome;Patients who received weight-loss supplements, antidepressants or hormonal medications during the past 3 months and during the study period;Patients with diabetic ketoacidosis or hyperosmolar non-ketoacidosis coma;Patients with an allergy to intervention drugs;Patients with severe hypertension (SBP>160 mmHg, DBP > mmHg);Patients with acute or chronic pancreatitis or pancreatic insufficiency.

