#### Rejection criteria

Those found in the middle of the trial who failed to meet the case selection criteria; failure to complete the diet exercise in accordance with the regulations; failure to use drugs as prescribed, unable to judge efficacy or providing incomplete information; taking drugs that were prohibited and may affect the judgement of the effect.

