#### Termination criteria

Subjects who withdraw informed consent and request withdrawal from the study; pregnancy events occur during the study; side effects of drug or treatment operations are still intolerable; a situation in which the researcher deems it necessary for study withdraw.

If the participant meets the rejection criteria, they are removed, and the data will not be included in the final statistical analysis. However, the termination criteria are related to patients who may terminate during treatment, so the data from these patients will be included in the final statistical analysis.

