### Statistical analysis

#### Population of statistical analysis

##### Full analytical set (FAS)

This term refers to the set including finished and shedding cases but excluding rejection cases. This group includes those who has taken at least one medication and were recorded in at least one follow-up.

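### The rejection rule has no cut-off at the end of treatment, so a prohibited drug started in follow-up can take a participant's completed end-of-treatment efficacy data out of the FAS

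*Protocol article*

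**What the plan says.** All references are to the protocol article.

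- **Ban and its period.** Under Drugs and usage (placebo combined with metformin group): "Other hypoglycemic, lipid-lowering or weight-loss drugs were not allowed to be used during the trial". The same paragraph gives the schedule: "The treatment will be conducted for 24 weeks and followed up for 24 weeks". The End of trial section closes the trial only when everyone has finished both periods.
- **Trigger.** Rejection criteria include "taking drugs that were prohibited and may affect the judgement of the effect". No time limit is attached.
- **Consequence.** Subject screening and selection: "If the patient meets one of the rejection criteria or termination criteria, they will be removed from the trial". The closing paragraph under Termination criteria: "If the participant meets the rejection criteria, they are removed, and the data will not be included in the final statistical analysis". The FAS is defined as "the set including finished and shedding cases but excluding rejection cases".
- **Role of the FAS.** The section on the safety analysis set adds that efficacy is analysed in the FAS and that conclusions rest chiefly on it.
- **When efficacy is judged.** The Primary outcome section gives the responder definition without an assessment time. The Discussion says follow-up serves to explore regain of weight and loss of improvement once the intervention stops. MRI fat is measured once before and once after treatment (Study design).
- **Metformin.** It is given up to the end of treatment (DDG combined with metformin group).

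**The concern.** Read together, these rules let an event in weeks 24 to 48 erase data that were complete at week 24. A drug taken in week 30 cannot alter an MRI measured at the end of treatment, yet the rule removes the participant's data as a whole and not only what follows the event.

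The trigger is foreseeable. Participants enter untreated, with fasting glucose still above 7.0 mmol/L after two weeks of diet and exercise (Inclusion criteria). Scheduled metformin ends with treatment, and other glucose-lowering drugs stay banned for a further 24 weeks. Those who then need a drug are likely to be those who responded poorly or relapsed. Exclusion would depend on something that happens after randomisation and is plausibly linked to outcome, in the set that carries the main conclusions. It could also remove some of the relapse that follow-up is meant to show.

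Membership of the FAS would partly rest on judgement. The Drop out criteria cover people who quit because treatment was ineffective, and dropouts stay in the FAS. Two participants with a similar course could be classified differently.

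**Working it through.** **Step 1: does the ban reach follow-up?** It runs for the duration of the trial, and both its own paragraph and End of trial count follow-up as part of that. The Exclusion criteria use two windows: one item reads "Patients who received weight-loss supplements, antidepressants or hormonal medications during the past 3 months and during the study period", another "Patients who receive other therapies or whose doses have changed during treatment". Narrower wording was available. This is supporting evidence only, since that list concerns eligibility.

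**Step 2: is rejection confined to the treatment period?** Not by any stated rule. The one sentence that retains data from before a change of treatment or death concerns severe adverse reactions and sits in the safety-set section.

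**Step 3: does the second half of the rejection condition close the gap?** It requires that the drug might influence the efficacy judgement. If that judgement is made only at week 24, a later drug cannot meet the condition. If it includes follow-up, as the Discussion suggests, it can. The Primary outcome section does not say which, so the assessor decides.

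**Step 4: how large could the effect be?** The plan gives no rate of drug starts and no figure on this point to reproduce. The only input from the document is 133 per arm (Abstract). Everything else is assumed: a week-24 primary outcome, every start leading to rejection, true response p = 45% v 30%, and r = 10% of responders starting a drug. Let s be the share of non-responders who start one.

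Response rate after deletion = p(1−r) / [p(1−r) + (1−p)(1−s)]

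Number deleted per arm = 133 × [p·r + (1−p)·s]

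Equal s in both arms:

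| s | Rates after deletion | Difference (points) | Deleted of 266 |
|---|---|---|---|
| 10% | 45.0% v 30.0% | 15.0 | 26.6 |
| 20% | 47.9% v 32.5% | 15.4 | 43.2 |
| 30% | 0.405/0.790 = 51.3% v 0.270/0.760 = 35.5% | 15.7 | 59.9 |
| 40% | 55.1% v 39.1% | 16.0 | 76.5 |
| 50% | 59.6% v 43.5% | 16.0 | 93.1 |

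The standard error of the difference is √[(0.45×0.55 + 0.30×0.70)/133] = 5.87 points with no deletion. At s = 30% in both arms it is 6.81 points.

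Unequal s (intervention v control), true difference 15.0:

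- 27.5% v 32.5%: 0.405/0.80375 = 50.4% v 0.270/0.7425 = 36.4%. The difference is 14.0, an error of −1.0.
- 32.5% v 27.5%: 0.405/0.77625 = 52.2% v 0.270/0.7775 = 34.7%. The difference is 17.4, an error of +2.4.

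A second assumed case has only non-responders starting drugs, 10% v 20%, with true response 50% v 35%:

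- The rates become 0.50/0.95 = 52.6% v 0.35/0.87 = 40.2%, so 15.0 points falls to 12.4. About 7 and 17 people are deleted.
- With equal true response of 40%, the same start rates give 0.40/0.94 = 42.6% v 0.40/0.88 = 45.5%, a spurious −2.9 points.

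**The case against.** The best defence is the qualifier in the rejection criterion. On its natural reading, a drug started after week 24 cannot influence a week-24 result, so such a person would not be rejected on that account. This also weakens the illustration: a week-24 primary outcome and rejection at every start fit together badly, so its deletion counts are an outer case. This stands as a limit on likelihood. It does not close the route, because no text ties the judgement to week 24.

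The time wording may be loose. The paragraph with the ban also has unused tablets returned at follow-up visits, although metformin stops with treatment, so its use of follow-up seems to include treatment visits. The neighbouring rejection items mainly concern conduct on treatment. That makes an unintended breadth plausible, which is a reason to state the cut-off.

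Three stronger readings are tempting, and the document supports none of them:

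- **That the plan deletes everyone who starts a drug in follow-up.** It permits deletion; it does not require it in every case. Some would be dropouts and stay in the FAS.
- **That resuming metformin triggers rejection.** The ban is on other glucose-lowering drugs, most naturally meaning other than the study drugs, and the text does not settle the point. If metformin is allowed, fewer people are exposed to the rule.
- **That safety data are lost too.** The safety set has its own definition and may keep them.

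The broader practice of excluding rejection cases from the FAS is a larger question. The present point is narrower: even someone who accepts that practice for violations during treatment gains nothing by discarding values that precede the violation.

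**Conclusion.** The point holds as a defect of wording that leaves a discretionary exclusion open. A participant who completes treatment and then starts a banned drug can be rejected and lose all efficacy data from the FAS, including values the drug could not have affected.

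Size and direction cannot be derived from the document. Under the assumed rates, the contrast barely moves when non-responders in the two arms start drugs equally often; the cost is then mainly precision and inflated response rates in both arms. Distortion needs start rates that differ between arms: −1.0 or +2.4 points for a 5-point gap around 30%, and −2.6 points in the 10% v 20% case. A reader might infer that the primary result is materially biased; nothing in the document shows that.

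The conclusion about wording rests on the article text alone. The participant schedule figure is not shown, and the full protocol may be more precise.

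**What to change.** Under Rejection criteria, and in the paragraph on their consequence at the end of Termination criteria, state that a drug started after the end-of-treatment (week-24) assessment is not a rejection criterion and that the participant's end-of-treatment data stay in the FAS.

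The cost is one or two sentences, with no added visits, measurements or participants. How week-48 values are handled after a newly started drug is a separate choice of estimand and not part of this change.

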## Data collection and management

### Data collection

Data will be collected from the daily symptom records recorded by the participants, the CRF recorded by the medical staff of the trial group and the medical records of the patients. Study data will be collected and managed using REDCap electronic data capture tools hosted at LongHua Hospital Shanghai University of Traditional Chinese Medicine. REDCap (Research Electronic Data Capture) is a secure, web-based software platform designed to support data capture for research studies that provides (1) an intuitive interface for validated data capture, (2) audit trials for tracking data manipulation and export procedures, (3) automated export procedures for seamless data downloads to common statistical packages, and (4) procedures for data integration and interoperability with external sources [20, 21].

### Data entry and data query forms

Data entry and administration are the responsibility of the assigned data administrator, who will establish the database and the validation programme. The data are then entered and confirmed by two professionally trained keyboard operators. After checking the CRF, the identified input errors will be corrected until the input data are identical to the CRF. Any queries on the CRF will be communicated to the investigator via a data query table. These data query tables must be processed, signed and dated by the researcher in a timely manner. The resolved data problem must be returned to the data manager, which will modify and validate the data based on the feedback, update the database accordingly, and then query the necessary data problem table again.

### Database locking

After confirming the accuracy of the established database by blind checking, the database will be locked. The locked data cannot be changed. If any data revisions are required after locking, an official statement signed jointly by the applicant, principal investigator, experimental project manager, statistician and data manager must be provided. In addition, revisions will be made in the statistical analysis [17].

## Evaluation

### Primary outcome

Effective rate of a 1% decrease in HbA1c and 3% decrease in body weight.

### Secondary outcome

Waist circumference, BMI, FPG, blood lipids, C-peptides, insulin, inflammatory factors, insulin resistance index (HOMA-IR)[HOMA-IR = FPG (mmol/L) × FINS (mIU/L)/22.5], and the subcutaneous and visceral fat contents of the upper abdomen will be measured by MRI.

### Security outcome

Routine blood tests, routine urine tests, routine stool tests, liver and kidney function tests, and EKG.

### Adverse events observation and recording

Upon entering the clinical trial, the patient’s vital signs, symptoms and any adverse events of disease or laboratory parameters will be recorded. The occurrence of adverse events is not necessarily related to the study drug. Adverse events were classified into three grades: mild, moderate and severe. Serious adverse events occur when the agent (1) results in death; (2) endangers life; (3) results in hospitalization or prolonged hospitalization; (4) causes deformities or birth defects; (5) causes permanent disability or (6) causes cancer. All serious adverse events were reported to the State Food and Drug Administration, Sponsor and Ethics Committee within 24 h. Any causal relationship between adverse events and the drug under this study will be determined by classification.

If a participant has a serious adverse event, the specific condition of the drug use must be known, and unblinding should only be performed with the consent of the principal investigator. Once reading the emergency letter, the case will be considered shedding.

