The study aims to recruit 266 participants (4 units in total). The four units include the following major leading and undertaking units. The Longhua Hospital affiliated with Shanghai University of traditional Chinese Medicine, which will recruit 86 participants. The remaining participating units will recruit 60 participants each: Yueyang Hospital of Integrated Chinese and Western Medicine affiliated with Shanghai University of traditional Chinese Medicine; Shanghai Jinshan Hospital of Integrated Chinese and Western Medicine; Shanghai Pudong New District People’s Hospital. Each unit is responsible for the specific responsibilities of the study, including recruiting patients and collecting specimens and data. Laboratory testing and imaging examination will be performed in the corresponding departments of each unit. Data analysis will be performed at the Clinical Research Center of Longhua Hospital affiliated with Shanghai University of Traditional Chinese Medicine.

To ensure the safety of the participants, blinding, data quality, and adherence to the study protocol, personnel directly participating in this study will be completely trained and will follow Good Clinical Practice (GCP) guidelines.

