#### Drop out criteria

Patients who must stop medication because of serious adverse drug reactions; patients who quit the trial due to ineffective treatment; patients who are unwilling to accept treatment or unable to complete follow-up due to poor compliance; patients who have no adverse reactions during treatment, but the treatment is interrupted due to other reasons, such as emigration and missing visits.

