### Blinding

The random distribution system will be implemented and managed by the Clinical Research Center of Longhua Hospital affiliated with Shanghai University of Traditional Chinese Medicine. The randomization code will be maintained by a specially appointed independent custodian. Researchers, participants, inspectors and data inputters will all be blind. The drug will be randomly coded according to the random scheme, and the coding number will become the unique identification code of the participants. According to the order of visits, subjects will be randomly divided into different groups. The dosage form and dose of the tested drug and the placebo are the same, and the drug will be uniformly packaged in the same drug label and distributed by the centre. The DDG placebo is prepared by the same manufacturer to ensure that the researchers and the patients do not have direct contact with the drug preparation and delivery process, so the double-blind method can be guaranteed. All participants and researchers in the trial will be asked to complete a questionnaire to evaluate the treatment at the last visit to assess the success rate of blinding [17].

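### Reading the emergency letter automatically makes a participant a drop-out, although a code break prevents no later measurement

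*Protocol article*

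**What the plan says.** The section on adverse events observation and recording first says that, after a serious adverse event, the participant's drug use has to be known. It then adds two rules: "unblinding should only be performed with the consent of the principal investigator. Once reading the emergency letter, the case will be considered shedding".

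Other sections bear on these rules:

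- **Drop out criteria.** The reasons listed are stopping medication for a serious adverse drug reaction, leaving because treatment does not work, refusing treatment or failing follow-up through poor compliance, and interruption for other reasons. A code break is not listed.
- **Full analytical set.** "This term refers to the set including finished and shedding cases but excluding rejection cases". At least one dose and one recorded follow-up are also required.
- **Safety analysis set, and the paragraph after it.** For severe reactions or death, the data kept for analysis are those from before the treatment change or the death. Missing safety values are not carried forward. Other missing data are filled by LOCF, and conclusions rest mainly on the FAS.
- **Study design (text with Fig. 1).** After the last treatment every patient goes into monthly follow-up.
- **Discussion.** Safety indices are to be monitored before, during and after treatment.
- **Blinding.** "The randomization code will be maintained by a specially appointed independent custodian".

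**The concern.** Unblinding changes what is known about a participant. It does not change whether that participant can be weighed, give blood or have an adverse event followed to its end. A rule that turns the code break itself into a drop-out confuses the two. The people it reaches have had a serious event, and for them both the course of the event and the later outcome matter most.

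If sites treat a shedding case as finished with the trial, later values will be missing. The primary outcome (the effective rate on HbA1c and body weight) would then be carried forward rather than observed, and later safety values would simply be absent. The trigger is harm. If serious events differ between arms, the missing data would differ too, and the comparison would be affected in a way that LOCF does not repair.

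**Working it through.** The article gives no count of expected code breaks, so there is no planned figure to reproduce. The check sets the texts side by side and then bounds the effect of one case.

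**Step 1: what shedding means.** The article does not define the word outright. The FAS definition joins shedding cases to finished ones as two different kinds, so a shedding case is one that did not finish. The rule "Once reading the emergency letter, the case will be considered shedding" therefore classes an unblinded participant as a non-completer.

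**Step 2: is a code break a drop-out reason elsewhere?** Each listed criterion describes someone who stops treatment, leaves or misses follow-up. The nearest is "Patients who must stop medication because of serious adverse drug reactions". It depends on stopping medication and applies whether or not the code is opened. The letter rule therefore adds those whose code is read but who meet none of the listed reasons.

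**Step 3: does the label fit the follow-up text?** The study design section sends every patient into post-treatment follow-up, and the discussion promises safety monitoring through and after treatment. Neither makes an exception for unblinded participants, and the adverse-event section does not say that their visits continue. The texts are unreconciled, and a site could follow either.

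**Step 4: what happens to the data?**

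- *Visits stop.* Later HbA1c and weight are missing and LOCF supplies them. Later safety values stay missing.
- *Visits continue but treatment has changed after a severe reaction.* The safety-set paragraph keeps data from before the change, so later values appear to be set aside.
- *Visits continue and treatment is unchanged.* Nothing is lost, and the shedding label serves no purpose.

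The article schedules blood biochemistry every 3 months during treatment. Assume that HbA1c follows that schedule and that the outcome is judged at the end of treatment; Fig. 2, which would show this, is not available. If measurement ceased before month 3, the baseline HbA1c would be carried forward, the change would be zero and the participant would count as a non-responder. If it ceased between months 3 and 6, the month-3 value would stand in for month 6.

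**Step 5: bound per case.** With 133 per arm, k carried-forward participants in one arm can move that arm's response rate by at most k/133. The values of k are illustrative only.

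| k in one arm | Largest shift |
|---|---|
| 1 | 1/133 = 0.8 percentage points |
| 3 | 3/133 = 2.3 percentage points |
| 5 | 5/133 = 3.8 percentage points |

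**Step 6: the consent condition.** One sentence says that drug use must be known after a serious event and also that "unblinding should only be performed with the consent of the principal investigator". Four centres recruit. As worded, the need to know and the word *only* can pull against each other, and the article does not say which prevails.

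**The case against.** The strongest reply is that the harm is inferred. A reader might conclude that follow-up ends at unblinding, but no sentence says so. Shedding cases remain in the main efficacy set, every patient is to enter follow-up, and anyone treated with documented safety data is in the safety set. LOCF acts only where data are missing. Many participants with serious drug reactions would be drop-outs anyway because they stop medication, so the added loss is smaller than the total. All of this stands, and it limits the point to a mislabelling that invites loss.

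A reader might also infer that emergency care will be delayed because one person must be reached from four hospitals. The article does not support that. It does not say whether each centre has its own principal investigator, how consent is given or whether a deputy exists; such steps may be in the full protocol, which is not shown. A consent step is also a legitimate control on needless code breaks. What stands is the tension within the sentence.

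Nor can the size be read from nearby figures:

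- The three non-lead centres hold 3 × 60 = 180 of 266 participants (68%). That matters only if consent sits at the lead centre.
- The earlier study of 80 people over 13 weeks reported no serious adverse effects. Treated as 0/80, the one-sided 95% upper limit is 1 − 0.05^(1/80) = 3.7%. That concerns events rather than opened letters, in people who all took DDG.
- A loss of 48 weeks of data would need unblinding at the very start and an end to visits.

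The reply does not remove the rule itself. It is stated in the article, so it is not a detail left to a fuller document.

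**Conclusion.** The point holds in a limited form. The plan classes a participant as a non-completer merely because the code was read. That has no basis in what can still be measured, is absent from the drop-out criteria and sits badly with the follow-up and safety-monitoring text. The consequence is a risk of missing outcomes triggered by serious events, and so possibly informative, with efficacy values filled by LOCF and safety values left blank. It is not established that follow-up stops.

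The number affected is probably small and cannot be derived from the article; the bound is about 0.8 percentage points in an arm's response rate per affected participant. This rests on reading shedding as the opposite of finished, and on some sites acting on that label. The gain from correcting it lies mainly in knowing the outcome of serious events and in avoiding avoidable, harm-related gaps.

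The consent condition supports only a request to reconcile the wording.

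**What to change.** 1. In the section on adverse events observation and recording, delete the automatic shedding rule. State that an unblinded participant remains in the study for all scheduled safety and efficacy assessments, that the event is followed to its outcome, and that the unblinding is recorded. At most, make unblinding a reason for exclusion from the per-protocol set.
2. Align the drop-out criteria, the FAS definition and the safety-set paragraph. Define shedding, and say how values observed after unblinding or after a treatment change are used, so that LOCF does not replace values that were measured.
3. Reconcile the statement that drug use must be known after a serious event with the consent condition, so that consent cannot block a code break that is needed. The mechanism is for the sponsor to settle.

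The cost is a few sentences and site training, a little extra follow-up, and some later assessments made with the allocation known. The unblinding record lets the analysis identify those assessments.
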